## 4.2 SCIENTIFIC RATIONALE FOR STUDY DESIGN

### Stage 1: safety run-in

Cetuximab and pembrolizumab have been extensively assessed in prior clinical trials both as monotherapy and in combination with chemotherapy and/or other targeted agents. Avelumab (anti-PD-L1) and cetuximab are being evaluated in an ongoing phase II study in patients with previously treated mCRC and preliminary results suggest the combination is effective and well-tolerated. Evorpaccept (ALX148) has been previously evaluated in phase I clinical trials in other cancer types, both as monotherapy and in combination (including with pembrolizumab, where it has been found to be well-tolerated). We are unaware of any studies that have previously combined evorpaccept (ALX148) (or any SIRP $\alpha$ /CD47 inhibitor), cetuximab (or any EGFR inhibitor), and pembrolizumab (or any anti-PD-(L)1 drug).

### Stage 2: dose expansion

Additional patients will be enrolled and treated with evorpaccept (ALX148), cetuximab, and pembrolizumab to better assess the efficacy and safety of this regimen. Additionally, a subset of patients (Cohort A) will undergo paired pre-treatment (after screening but before C1D1) and on-treatment (around C3D1) biopsies. This will allow for exploration of changes in tumor infiltrating immune cells (both innate and adaptive) and if this may be predictive or prognostic. The two cohorts (Cohort A and Cohort B) otherwise are identical and receive the same treatment.

Patients will not be randomized between the two cohorts and rather can enroll based on slot availability and Investigator/patient preference.

### 4.3 JUSTIFICATION FOR DOSE

Evorpaccept (ALX148) dosing is based on prior phase I data in which no MTD was reached alone or in combination (maximum administered dose 15 mg/kg weekly with pembrolizumab and chemotherapy and 15 mg/kg weekly with rituximab and trastuzumab Cetuximab and pembrolizumab dosing is based on standard dosing.

Specifically for pembrolizumab, the planned dose of pembrolizumab for this study is 200 mg every 3 weeks (Q3W). Based on the totality of data generated in the Keytruda development program, 200 mg Q3W is the appropriate dose of pembrolizumab for adults across all indications and regardless of tumor type. As outlined below, this dose is justified by:

- Clinical data from 8 randomized studies in melanoma and NSCLC indications demonstrating flat dose- and exposure-efficacy relationships from 2 mg/kg Q3W to 10 mg/kg Q2W, representing an approximate 5- to 7.5-fold exposure range (refer to IB, Section 5.2.2)
- Population PK analysis showing that both fixed dosing and weight-based dosing provides similar control of PK variability with considerable overlap in the distributions of exposures, supporting suitability of 200 mg Q3W
- Clinical data showing meaningful improvement in benefit-risk including overall survival at 200 mg Q3W across multiple indications, and
- Pharmacology data showing full target saturation in both systemic circulation (inferred from pharmacokinetic [PK] data) and tumor (inferred from physiologically-based PK [PBPK] analysis) at 200 mg Q3W

### 4.4 END OF STUDY DEFINITION

Patients in both the safety run-in and dose expansion stages will continue to receive study therapy until disease progression according to RECIST v1.1, unacceptable toxicity, death, patient or physician decision to withdraw, or pregnancy, whichever occurs first. Criteria in which patients in all cohorts may continue treatment after radiographic progression are detailed in Section 4.1.2. The end of study will be considered to have occurred when the 90-day phone call following the Final Study/Treatment Discontinuation Visit is complete. Overall survival information will be collected via telephone calls and/or clinic visits every 3 months  $\pm$  14 days (first call and/or clinic visit to occur 3 months following the Final Study/Treatment Discontinuation Visit) until death, withdrawal of consent, the patient is lost to follow-up, study termination by AGICC, or a maximum of 2 years from the Final Study/Treatment Discontinuation Visit.

## 5 STUDY POPULATION

### 5.1 INCLUSION CRITERIA

To be eligible to participate in this study, an individual must meet all of the following criteria at screening (any assessments included in the Schedule of Events [Section 1.3] on Cycle 1 Day 1 must also continue to be met for the patient to remain eligible):

1. Provision to sign and date the consent form.
2. Able to comply with all study procedures and be available for the duration of the study in the Investigator's judgment.
3. Age  $\geq 18$  years on the day of signing informed consent
4. If in Cohort A, the patient must state willingness to undergo pre- and post-treatment biopsies. According to the Investigator's judgement, the planned biopsies should not expose the patient to substantially increased risk of complications.
5. Eastern Cooperative Oncology Group (ECOG) performance status of 0 or 1.
6. Histologically confirmed unresectable metastatic colorectal adenocarcinoma.
  - All primary tumor locations are allowed
  - Measurement of EGFR expression by immunohistochemistry is not required
7. Progression on at least two prior lines of therapy for unresectable metastatic colorectal adenocarcinoma.
  - A patient who progressed on a single line of therapy including a fluoropyrimidine, oxaliplatin, and irinotecan for unresectable metastatic colorectal adenocarcinoma (e.g., FOLFIRINOX or FOLFOXIRI) is eligible.
  - Previous administration of anti-EGFR drugs does not impact eligibility, except as listed in Exclusion Criterion #15.
8. Microsatellite stable or proficient mismatch repair status documented (only one of these criteria is needed, however if one criterion is met and one is not met then the patient is excluded)
9. Measurable disease, according to RECIST v1.1. Previously irradiated lesions are not considered measurable unless progression has been documented in the lesion. Note that lesions intended to be biopsied should not be target lesions.
10. Adequate hematologic and end organ function, defined by the following laboratory results:
  - $ANC \geq 1.5 \times 10^9/L$
  - Platelet count  $\geq 100 \times 10^9/L$
  - Hemoglobin  $\geq 9$  g/dL without transfusion in the previous week
  - Serum bilirubin  $\leq 1.5 \times$  the upper limit of normal (ULN); patients with known Gilbert's disease may have a bilirubin  $\leq 3.0 \times ULN$

- AST, ALT, and alkaline phosphatase (ALP)  $\leq 3 \times \text{ULN}$  with the following exceptions:
    - Patients with documented liver metastases: AST and/or ALT  $\leq 5 \times \text{ULN}$
    - Patients with documented liver or bone metastases: ALP  $\leq 5 \times \text{ULN}$
  - Creatinine clearance  $\geq 50 \text{ mL/min}$  as calculated using the Cockcroft-Gault formula or measured using a 24-hour urine collection
  - International normalized ratio (INR) OR prothrombin time (PT)  $\leq 1.5 \times \text{ULN}$  unless participant is receiving anticoagulant therapy as long as INR or PT is within expected or therapeutic range of intended use of anticoagulants
  - Activated partial thromboplastin time (aPTT)  $\leq 1.5 \times \text{ULN}$  unless participant is receiving anticoagulant therapy as long as aPTT is within expected or therapeutic range of intended use of anticoagulants
11. QTcF interval of  $\leq 480 \text{ msec}$  (Based upon value from the screening ECG).
12. Serum pregnancy test (for females of childbearing potential) negative at screening and at C1D1. A woman is considered fertile (woman of childbearing potential, “WOCBP”) following menarche and until becoming post-menopausal unless permanently sterile. Women in the following categories are not considered WOCBP:
- Premenarchal
  - Premenopausal female with one of the following: documented hysterectomy, documented bilateral salpingectomy, documented bilateral oophorectomy (note: documentation can come from the site personnel’s review of the participant’s medical records, medical examination, or medical history interview)
  - Postmenopausal female. A postmenopausal state is defined as no menses for 12 months without an alternative medical cause. A high follicle stimulating hormone (FSH) level in the postmenopausal range may be used to confirm a postmenopausal state in women not using hormonal contraception or hormonal replacement therapy (HRT). However, in the absence of 12 months of amenorrhea, confirmation with two FSH measurements in the postmenopausal range is required. Females on HRT and whose menopausal status is in doubt will be required to use one of the non-hormonal highly effective contraception methods if they wish to continue their HRT during the study. Otherwise, they must discontinue HRT to allow confirmation of postmenopausal status before study enrollment.

Female participants of childbearing potential are eligible to participate if they agree to correctly use one of the following forms of highly effective method of contraception with a failure rate of  $<1\%$  per year when used consistently and correctly during the treatment period and for at least 180 days after the last study treatment. Periodic abstinence (e.g., calendar, ovulation, symptothermal, or postovulation methods) and

withdrawal are not acceptable methods of contraception. Use should be consistent with local regulations regarding the use of contraceptive methods for participants of clinical studies. If locally required, in accordance with Clinical Trial Facilitation Group (CTFG) guidelines, acceptable hormonal contraceptives are limited to those which inhibit ovulation.

- Progestogen- only contraceptive implant
- Intrauterine hormone-releasing system
- Intrauterine device (IUD)
- Bilateral tubal occlusion
- Vasectomized partner. A vasectomized partner is a highly effective contraception method provided that the partner is the sole male sexual partner of the WOCBP and the absence of sperm has been confirmed. If not, an additional highly effective method of contraception should be used.
- Sexual abstinence. Sexual abstinence is considered a highly effective method only if defined as refraining from heterosexual intercourse during the entire period of risk associated with the study treatment. The reliability of sexual abstinence needs to be evaluated in relation to the duration of the study and the preferred and usual lifestyle of the participant.
- Combined (estrogen- and progestogen- containing) hormonal contraception, including oral, intravaginal, transdermal, or injectable
- Progestogen-only hormonal contraception, including oral or injectable

13. For men: Male participants with female partners of childbearing potential are eligible to participate if they agree to one of the following during the treatment period and for at least 180 days after the last dose of study treatment as defined below. Periodic abstinence (e.g., calendar, ovulation, symptothermal, or postovulation methods) and withdrawal are not acceptable methods of contraception. Men must also agree to refrain from donating sperm following during the treatment period and for at least 180 days after the last dose of study treatment.

- Be abstinent from penile-vaginal intercourse as their usual and preferred lifestyle (abstinent on a long term and persistent basis) and agree to remain abstinent
- Use a male condom plus partner use of a contraceptive method with a failure rate of <1% per year as described in Inclusion Criteria #12 when having penile-vaginal intercourse with a woman of childbearing potential who is not currently pregnant.
  - Note: Men with a pregnant or breastfeeding partner must agree to remain abstinent from penile-vaginal intercourse or use a male condom during each episode of penile penetration.

## 5.2 EXCLUSION CRITERIA

An individual who meets any of the following criteria will be excluded from participation in this study:

Cancer-related exclusion criteria:

1. Patients with known MSI-high status or known mismatch repair deficiency (dMMR)
2. Patients in whom both mismatch repair and microsatellite stability status are unknown
3. Has known active CNS metastases and/or carcinomatous meningitis. Participants with previously treated brain metastases may participate provided they are radiologically stable, i.e. without evidence of progression for at least 4 weeks by repeat imaging (note that the repeat imaging should be performed during study screening), clinically stable and without requirement of steroid treatment for at least 14 days prior to Cycle 1 Day 1.
4. Systemic anti-cancer therapy within 4 weeks of starting study treatment (6 weeks for mitomycin C or nitrosureas). If systemic anti-cancer therapy was given within 4 weeks, patient may be included if 5 times the elimination half-life of the drug has passed.
5. Malignancies other than CRC within 3 years prior to Cycle 1 Day 1 with the exception of those with a negligible risk of metastasis or death (e.g., expected 5-year overall survival > 90%) treated with expected curative outcome (such as adequately treated carcinoma in situ of the cervix, basal or squamous cell skin cancer, localized prostate cancer treated surgically with curative intent, and ductal carcinoma in situ treated surgically with curative intent).
6. Prior radiation therapy within 14 days prior to study Cycle 1 Day 1 and/or persistence of radiation-related adverse effects. Participants must have recovered from all radiation-related toxicities, not require corticosteroids, and not have had radiation pneumonitis. A 1-week washout is permitted for palliative radiation ( $\leq 2$  weeks of radiotherapy) to non-CNS disease. However, palliative radiation therapy (as long as it does not involve target lesions) is permitted on the study.
7. Prior allogeneic bone marrow transplantation or solid organ transplant for another malignancy in the past.
8. Spinal cord compression not definitively treated with surgery and/or radiation.
9. Uncontrolled pleural effusion, pericardial effusion, or ascites requiring recurrent drainage procedures.
10. Uncontrolled tumor related pain. Patients who require narcotic pain medication during screening should be on a stable dose regimen for seven days prior to Cycle 1 Day 1.

Exclusion criteria related to study medication:

11. History of severe allergic, anaphylactic, or other hypersensitivity reactions to any of the study medications or their classes
12. History of red meat allergy or history of tick bite (these may increase the risk of a cetuximab infusion reaction).

13. Prior therapy with an anti-PD-1, anti-PD-L1, or anti-PD-L2 agent or with an agent directed to another stimulatory or co-inhibitory T-cell receptor (eg, CTLA-4, OX-40, CD137).
14. Prior treatment with any anti-CD47 or anti-SIRP $\alpha$  drugs
15. Left-sided (at or distal to the splenic flexure) RAS/BRAF WT mCRC who are EGFR inhibitor naïve.
16. Has a diagnosis of immunodeficiency or is receiving systemic steroid therapy or any other form of immunosuppressive therapy within 7 days prior to Cycle 1 Day 1.
17. History of hemolytic transfusion reaction.
18. History of non-infectious pneumonitis/interstitial lung disease that required steroids or has current pneumonitis/interstitial lung disease.
19. Has an autoimmune disease that has required systemic treatment in the past 2 years with use of disease modifying agents, corticosteroids, or immunosuppressive drugs. Replacement therapy (eg; thyroxine, insulin, physiologic corticosteroid replacement therapy for adrenal or pituitary insufficiency) is not considered a form of systemic treatment.
20. History of autoimmune hemolytic anemia or autoimmune thrombocytopenia

Exclusion criteria based on organ function or medical history:

21. Any major surgery within 28 days prior to enrollment (does not include pre-treatment biopsy).
22. The patient has clinically relevant coronary artery disease or history of myocardial infarction in the last 12 months or high risk of uncontrolled arrhythmia or uncontrolled cardiac insufficiency.
23. The patient has uncontrolled or poorly-controlled hypertension (>180 mmHg systolic or > 130 mmHg diastolic).
24. Life expectancy of < 12 weeks.
25. Has a history or current evidence of any condition, therapy, or laboratory abnormality that might confound the results of the study, interfere with the participant's participation for the full duration of the study, or is not in the best interest of the participant to participate, in the opinion of the treating investigator.
26. Has known psychiatric or substance abuse disorders that would interfere with cooperation with the requirements of the trial.
27. Pregnant or lactating or intending to become pregnant during the study.
28. AEs due to prior cancer therapies that have not returned to  $\leq$ Grade 1 or baseline. Participants with endocrine-related AEs Grade  $\leq$ 2 that are now controlled with treatment/hormonal therapy are eligible.

Exclusion criteria based on infectious diseases:

29. Active infection requiring IV antibiotics at screening.

30. Patients with active hepatitis B (chronic or acute). Active hepatitis B infection is defined as having a positive hepatitis B surface antigen [HBsAg] test at screening. Patients with a cleared hepatitis B infection (as defined by the presence of hepatitis B core antibody [anti-HBc], absence of HBsAg, and negative HBV DNA) are eligible.
31. Patients with active hepatitis C. Patients positive for hepatitis C virus (HCV) antibody are eligible only if polymerase chain reaction (PCR) is negative for HCV RNA.
32. Known HIV infection.
33. Recent COVID-19 diagnosis (symptomatic or asymptomatic). To become eligible (following symptomatic infection), the patient must not have fever for 24 hours (without using medicine to reduce fever), other symptoms have improved, and at least 10 days have passed since onset of symptoms. To become eligible (following asymptomatic infection, ie positive test only), at least 10 days have passed since the positive test. In either case, a repeat COVID-19 test is not required. Likewise, a persistently positive test (if obtained) does not continue to exclude the patient should the other criteria be satisfied.
34. Influenza vaccination should be given during influenza season. Patients must not receive live, attenuated influenza vaccine (e.g., FluMist®) within 30 days prior to Cycle 1 Day 1 or at any time during the study and for at least 5 months after the last dose of study drug.

### 5.3 LIFESTYLE CONSIDERATIONS

There are no lifestyle considerations other than those pertaining to abstinence/contraception as outlined in section 5.1 (Inclusion Criteria).

### 5.4 SCREEN FAILURES

If in the determination of the PI there is reasonable chance that a patient may meet inclusion/exclusion criteria at a time following a screen failure, a patient may be re-screened for eligibility with documented approval from the medical monitor.

### 5.5 STRATEGIES FOR RECRUITMENT AND RETENTION

Potential subjects will be identified and recruited from the research study team's clinic. The consent process will be conducted in a private room. Potential subjects will be given a copy of the consent form to take home with them before making a final decision to participate. Advertisements approved by ethics committees and Investigator databases may be used as recruitment procedures. Patients will be recruited without regard to sex, race, or ethnicity.

In order to achieve a total sample size of 48 patients (including both Stage 1 and Stage 2), it is estimated that 56 patients will need to be screened (i.e., allowing for 4 patients who fail screening and 4 patients who do not complete the study). There will be approximately 5 sites (all

in the United States) involved, and it is estimated that the enrollment rate will be 1 patient/site/month. It will take approximately 12 months to fully enroll the study. The total study duration is anticipated to be approximately 24 months (enrollment/treatment) and 48 months (including survival follow-up).

## 6 STUDY INTERVENTION

### 6.1 STUDY INTERVENTION(S) ADMINISTRATION

#### 6.1.1 STUDY INTERVENTION DESCRIPTION

The study agents for this study are evorpacept (ALX148), cetuximab, and pembrolizumab.

Evorpacept (ALX148), cetuximab, and pembrolizumab packaging will be overseen by ALX Oncology Ltd, Eli Lilly USA, LLC, and Merck & Co, Inc. clinical trial supplies department, respectively, and will bear labels in compliance with US Federal law. The packaging and labeling of the study drugs will be in accordance with the manufacturer's standards and Federal regulations.

Upon delivery of the investigational products to the site, site personnel should check for damage and verify proper identity, quality, integrity of seals and temperature conditions. Site personnel should report any deviations or product complaints to the AGICC and/or ALX Oncology Ltd, Merck & Co, Inc., and Eli Lilly USA, LLC (as appropriate) upon discovery.

Evorpacept (ALX148), cetuximab, and pembrolizumab will be stored at the clinical site under the required storage conditions as indicated on the study drug labels.

#### 6.1.2 DOSING AND ADMINISTRATION

Evorpacept (ALX148), cetuximab, and pembrolizumab will all be given on an outpatient basis.

On administration days when dosing schedules coincide, evorpacept (ALX148) will be given first, followed by a 30-minute delay. Then, cetuximab and/or pembrolizumab should be given in an order determined by institutional standards.

Patients will be observed in the clinic for at least 2 hours after infusion of evorpacept (ALX148) on C1D1 and as clinically indicated thereafter.

Dose levels are provided in Section 12.1.2.

The maximum duration of pembrolizumab is 35 cycles. There is no maximum duration of evorpaccept (ALX148) or cetuximab.

## **Dose, administration, and premedication**

### *Evorpaccept (ALX148) (per the Investigator's Brochure)*

- Dose: 15 mg/kg day 1, 8, and 15 every 21 days
- Administration: Administer infusion solution intravenously over 60 minutes  $\pm$  10 minutes. The use of an infusion pump is the preferred method of administration to ensure accurate delivery of the investigational product, but gravity drips are allowed.
- Pre-medication: none required
- Route of administration: intravenous
- Starting dose and dose escalation: not applicable
- Dose adjustments/modifications/delays: see Appendix 1
- Duration of therapy: Patients in both the safety run-in and dose expansion stages will continue to receive study therapy until disease progression according to RECIST v1.1, unacceptable toxicity, death, patient or physician decision to withdraw, or pregnancy, whichever occurs first. Criteria in which patients in all cohorts may continue treatment after radiographic progression are detailed in Section 4.1.2.
- Tracking of dose: not applicable

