#### 4.1.3 STAGE 1: SAFETY RUN-IN

The original protocol (version 1, dated 12/22/21) specified that approximately six patients (no more than 18, accounting for the possible need for additional dose levels) will be accrued in Stage 1. A single patient will be treated with evorpacept (ALX148) 15 mg/kg weekly, cetuximab (400 mg/m^2 cycle 1 day 1 followed by 250 mg/m^2 weekly), and pembrolizumab (200 mg every 3 weeks), followed by a 48-hour safety observation period prior to treating the next patient. A 48-hour safety observation period will be required between the start of treatment for patients in Stage 1. One cycle will be 21 days. Evorpacept (ALX148) dosing is based on prior phase I data in which no maximum tolerated dose (MTD) was reached alone or in combination (maximum administered dose 15 mg/kg weekly with pembrolizumab and chemotherapy and 15 mg/kg weekly with rituximab and trastuzumab) and treatment was well tolerated. Cetuximab and pembrolizumab dosing is based on standard dosing. Once 6 patients have been enrolled into the study, further accrual to the study will be temporarily halted while the study team reviews the totality of the first-cycle clinical data to determine safety and tolerability of the regimen. The safety review should contain data from patients who have been receiving the regimen for a minimum of one cycle of treatment.

Further enrollment and study treatments will be halted if either of the following occur:

- Any patient experiences death due to an adverse event that is assessed as related to study treatment (by investigator and/or AGICC)
- At least 33% of patients experience a DLT

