### **Protocol amendment version 2 (dated December 28, 2022)**

During Stage 1 of this study, six patients were administered evorpacept (ALX148) 15 mg/kg, weekly in combination with pembrolizumab and cetuximab. One patient experienced a DLT of grade 5 HLH (see Section 2.3.1) that was assessed as possibly related to ALX148, pembrolizumab and cetuximab and the study was temporarily paused per protocol guidance. Three additional patients had completed the full DLT assessment period (all cycle 1 study treatments) and two additional patients did not complete all cycle 1 doses without reporting a DLT. Protocol amendments included in version 2 (dated December 28, 2022) dictate modification to Stage 1 when the study re-opens to enrollment in response to this event. Stage 1 will evaluate an additional patient cohort (N=3) administered evorpacept (ALX148) dose level -1 (10 mg/kg weekly) and dose level 1 of both cetuximab (400 mg/m^2 cycle 1 day 1 followed by 250 mg/m^2 weekly) and pembrolizumab (200 mg every 3 weeks). If there are no DLTs among these 3 patients, then N=3 additional patients will be enrolled at evorpacept dose level 1 (15 mg/kg weekly) with the same doses of cetuximab and pembrolizumab. If there is one DLT among the initial 3 patients enrolled at evorpacept (ALX148) dose level -1 (evorpacept 10 mg/kg), a further 3 patients will be enrolled at that dose level. Escalation to dose level 1 (evorpacept 15 mg/kg) should only be permitted if either 0 of 3 or 1 of 6 patients experience a DLT at evorpacept (ALX148) dose level -1. This follows a standard '3+3' study design at

ALX148 dose level -1 (evorpacept 10 mg/kg) upon re-initiation of the study. Consistent with protocol version 1, the study will proceed to Stage 2 at doses where less than 33% of patients experience a first-cycle DLT. See Figure 6 for additional details on the management of Stage 1 under protocol version 2. Note that in the event of a further DLT in 1 of 3 patients at evorpacept (ALX148) dose level 1 (evorpacept 15 mg/kg) i.e., 2 of 7 patients treated at dose level 1 (including N=4 patients treated under protocol version 1 dated 12/22/21), a complete safety evaluation including assessment of late onset toxicities should be reviewed by the data safety monitoring committee (DSMC) prior to proceeding to Stage 2. This DSMC review would be in addition to the DSMC review after N=12 patients in Stage 2 have been treated for at least one cycle as noted in Section 4.1.1.

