### 12.1.2 DOSE LEVELS

#### Evorpaccept (ALX148)

- Dose level 1: 15 mg/kg weekly
- Dose level -1: 10 mg/kg weekly
- Dose level -2: 5 mg/kg weekly

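### Section 6.1.2 states evorpacept 15 mg/kg for everyone, but Section 4.1.3 assigns 10 mg/kg to the cohort that restarts Stage 1 under version 2

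*Protocol*

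**What the plan says.** Section 6.1.2 gives a single evorpacept dose, "Dose: 15 mg/kg day 1, 8, and 15 every 21 days". The same entry adds "Starting dose and dose escalation: not applicable" and "Dose adjustments/modifications/delays: see Appendix 1", and its duration-of-therapy line applies to patients in both the safety run-in and the dose expansion. Earlier in the section the reader is told "Dose levels are provided in Section 12.1.2". That section lists 15, 10 and 5 mg/kg weekly as levels 1, -1 and -2 (for example "Dose level -1: 10 mg/kg weekly").

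Section 4.1.3 describes Stage 1 in two layers. The version 1 text starts everyone at the top level: "A single patient will be treated with evorpacept (ALX148) 15 mg/kg weekly". The version 2 text reports what happened: "One patient experienced a DLT of grade 5 HLH", assessed as possibly related to all three drugs. It then sets the restart: "Stage 1 will evaluate an additional patient cohort (N=3) administered evorpacept (ALX148) dose level -1 (10 mg/kg weekly"), expanded by 3 if one of the first 3 has a DLT. A return to 15 mg/kg depends on 0 of 3 or 1 of 6 patients having a DLT at 10 mg/kg. Section 4.1.4 treats Stage 2 patients at the RD, which is not fixed at 15 mg/kg.

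**The concern.** The dose line in 6.1.2 matches the version 1 starting dose and was not adapted to the version 2 restart. Because its entry covers the run-in as well as the expansion, it applies on its face to the restart cohort, for whom 4.1.3 assigns a lower dose. The statement that starting dose and escalation do not apply also fails to describe a restart at a reduced level with conditional escalation. That statement is identical for all three drugs and may be template text, so it only supports the point.

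What is at stake is patient safety and protocol consistency, not inference. Read literally, 6.1.2 gives a restart patient the dose level at which the fatal DLT occurred, before the escalation rule permits it. It would also cloud the DLT count at 10 mg/kg on which escalation depends, if any patient in that cohort were dosed at 15 mg/kg.

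**Working it through.** The check is mainly a comparison of texts; the plan states no figure here to reproduce.

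**1. Which dose applies to whom**

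| Patients | Section 6.1.2 | Sections 4.1.3 / 4.1.4 | Agree? |
|---|---|---|---|
| Stage 1, version 1 (6 treated) | 15 mg/kg | 15 mg/kg | Yes |
| Stage 1 restart, version 2 (3, or 3 + 3 = 6) | 15 mg/kg | 10 mg/kg | No |
| Stage 1, version 2, after escalation (3) | 15 mg/kg | 15 mg/kg | Yes |
| Stage 2 (42) | 15 mg/kg | RD | Only if RD = 15 mg/kg |

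**2. Whether the pointers in 6.1.2 resolve it**

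- Section 12.1.2 lists three levels and assigns none to a cohort.
- Appendix 1, which contains 12.1.2, concerns management of toxicity. Lower levels there are reductions for an individual patient who has had toxicity.
- Section 4.1.2, cited in the duration line, covers treatment beyond progression.
- Nothing in 6.1.2 refers to 4.1.3, where the restart dose is assigned.

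**3. Whether this is only a record of superseded text**

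No. The version 2 subsection of 4.1.3 is the rule for the re-opened study, and 6.1.2 is current dosing text.

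**4. Size of the dose difference**

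- Ratio: 15 / 10 = 1.5.
- Per infusion: 15 - 10 = 5 mg/kg extra.
- Per 21-day cycle of three weekly infusions: 3 × 15 = 45 mg/kg against 3 × 10 = 30 mg/kg.

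**5. What is known about 15 mg/kg in this regimen**

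Section 4.1.3 and the footnote to Figure 6 give 1 DLT among 4 DLT-evaluable patients treated under version 1.

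- Observed proportion: 1 / 4 = 25%.
- Exact (Clopper-Pearson) 95% limits: the lower is the 0.025 quantile of Beta(1, 4), which equals 1 - 0.975^(1/4) = 0.0063. The upper is the 0.975 quantile of Beta(2, 3) = 0.8059.
- Interval: 0.6% to 80.6%.

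So the data neither clear nor condemn the 15 mg/kg level. They give no comparison with 10 mg/kg.

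**The case against.** The strongest reply is that 6.1.2 lists nominal doses. The evorpacept entry is headed as following the Investigator's Brochure, and the other two as following the package insert. The cetuximab line likewise gives 250 mg/m² weekly without a qualifier, although 4.1.3 and 4.1.4 allow for a different dose. The section does tell the reader that dose levels exist, and 12.1.2 uses the same labels that 4.1.3 uses. Moreover, 15 mg/kg is not a discarded dose: it is still dose level 1, and version 2 aims to return to it. A site also cannot know that a patient belongs to the restart cohort without reading 4.1.3, which states 10 mg/kg.

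There are further safeguards. The Medical Monitor signs off each enrollment (Section 1.3 footnote 17 and Section 8.2.1), and dispensing follows a Pharmacy Manual (Section 6.2.4) that is not available for this review. Finally, the fatal event was attributed as possibly related to all three drugs, Section 12.1.12 notes hemophagocytic lymphohistiocytosis in fewer than 1% of patients given pembrolizumab, and 1 of 4 shows no excess risk from the extra 5 mg/kg.

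Much of this stands. It makes a dosing error less likely, and no excess risk of 15 over 10 mg/kg is demonstrated. It does not make the sections agree. The entry in 6.1.2 is not labelled nominal, it covers the run-in by its own duration line, and it gives no route to the section that assigns the dose. The Medical Monitor's approval, as described, is of the screening documents, and dose is not mentioned.

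**Conclusion.** The inconsistency is real and should be fixed. The dose stated in 6.1.2 is wrong for a defined group, the 3 to 6 patients of the version 2 restart cohort, by a factor of 1.5 and in the unsafe direction. It is right for patients later enrolled at dose level 1. It becomes wrong for the 42 Stage 2 patients only if the RD is below 15 mg/kg.

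The conclusion rests on the two current texts and needs no assumption about the size of the dose-toxicity relation. How likely an actual overdose would be cannot be judged from the protocol alone, because the Pharmacy Manual is not shown. The explicit wording of 4.1.3 suggests that most sites would dose correctly. No endpoint, hypothesis, error rate or sample size is affected.

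**What to change.** Make two changes to the evorpacept entry in Section 6.1.2:

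- Replace the dose line with: *the dose level assigned under Section 4.1.3 (Stage 1) or the RD (Stage 2), on days 1, 8 and 15 every 21 days*.
- Replace the not-applicable entry for starting dose and escalation with a reference to Section 4.1.3.

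The cost is a two-line text correction, issued as a clarification letter or with the next amendment. It adds no procedures and no patients.
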